### Participants and procedures

Figure 1; Table 1 present a flow chart detailing the enrollment, interventions and assessments.

**Fig. 1 Fig1:**
[figure not shown]
Flow chart of the PARI study

**Table Tab1:** Table 1 Shows the interventions in both the intervention and the control group at days 1, 3, 5, 7 and 15. They are further explained below

Evaluation	Day				
	**1**	**3**	**5**	**7**	**15**
**Inclusion, CRF, PCT measurement**	**x**				
**ARTIQ questionnaire**	**x**	**x**	**x**	**x**	**x**
**Telephone interview**			**x**		**x**

*CRF* Case Report Form, *ARTIQ* Acute Respiratory Tract Infection Questionnaire

Adult patients presenting to their GP with symptoms of ARTI will be recruited.

#### Inclusion criteria

The following inclusion criteria must be present:

Age $$\ge$$ 18 yearsAbility to read, understand and willingness to give written consent to participate in the study.Symptoms of acute upper/lower respiratory tract infection (pharyngitis, tonsillitis, otitis media, exacerbations of chronic obstructive pulmonary disease (COPD), or asthma and pneumonia).CRP > 20 mg/mL (based on POC-test in clinic)..

#### Exclusion criteria

If one or several of the following criteria are present, the participant will be excluded from the study:

The patient is being followed up by a hospital because of verified immune defect or the patient is currently neutropenic (neutrophils < 0,5 mia/L during the last 7 days).The patient has a positive strep A test, (only performed if indicated according to Centor criteria [23].The patient has been treated with antibiotics during the last 14 days up to inclusion.The doctor estimates that the patient needs to be admitted to hospital.The patient is pregnant or breastfeeding..

At any point, the GP will be able to overrule the PCT measurement in the intervention group based on clinical judgement. The reason for deviating from the suggested algorithm must be stated (see Fig. 2).

**Fig. 2 Fig2:**
[figure not shown]
Algorithm in case of deviation from the protocol intervention

#### Interventions and timeline

All participants will receive standard care as per the GPs’ normal procedures and treatments including POCT CRP testing. Patients randomized to the intervention/PCT group will additionally receive diagnostic testing with measurement of PCT.

#### Day 1

Following pre-inclusion assessment, including oral and written information about the PARI study, eligible patients must sign a consent form prior to participation. Subsequently, they will be randomized to either (i) the control group, or (ii) the PCT group. Data-gathering on day 1 will cover participant demographics, the current infection and the likely focus, duration of illness, and assumed etiological micro-organism, objective findings and CRP-level, and results of a self-reported acute respiratory tract infection questionnaire (ARTIQ). In addition, PCT values for the intervention group will be collected on day 1. The control group will receive standard care according to clinical guidelines [24, 25], and the intervention group will receive standard care *plus* PCT-guided treatment (see below).

#### Days 3 and 7

Each participant will be sent a link to the ARTIQ by e-mail on days 3 and 7 (it will also be available in hard copy if required, with responses collated by the investigator). The participants enter their responses into a database (Surveyxact). The content of the ARTIQ is presented in Appendix 1.

#### Days 5 and 15

All participants will be interviewed over the telephone to follow-up on their clinical condition (changes in general condition, fever, pain or coughing), days unable to work, the results of the ARTIQ, and compliance.

#### Day 30

An administrative follow-up to gather information about the use of antibiotics and hospital admissions.

### Outcomes

#### Primary outcome

Duration of illness and symptoms from an ARTI. The participant-reported primary outcome will be assessed as the number of days until a patient’s daily activities (e.g. work and recreation) are no longer restricted by symptoms from an ARTI. The non-inferiority margin between the intervention group and the control group is set at a one-day difference. The recovery measure will be the specific day indicated by the participants using the validated ARTIQ.

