## Methods/Design

### Design, setting and randomization

This study is a randomized, single-blinded, non-inferiority, multi-practice intervention study comparing a PCT group to a control group. We expect the mean duration of ARTI symptoms to be approximately 9 days [21, 22] and we want to detect if this increases to > 10 days in the PCT group i.e. a non-inferiority limit of one day.

The PARI project is a single-blinded study as participants will not be informed of their allocation group: standard care or PCT group. GPs will have access to the PCT results for the intervention group. GPs can tell patients if the biomarker suggests whether antibiotics are needed or not. This is based on the CRP results for both groups and, in the intervention group only, also the PCT levels. Patients will be informed only that “the biomarker” suggests relevant treatment, and other similar generic statements; they will not be informed as to which biomarker the physician refers.

In case of accidental demasking, the investigator will report this as a protocol deviation.

If the PCT level is above 2 ng/L, demasking will deliberately take place because the GP will have to consider referring the patient to hospital on suspicion of serious infection.

At least five practices in two different regions of Denmark, The Capital Region and Region Zealand, will recruit participants, representing both urban and rural areas.

Randomization will be performed by a remote internet-based randomization tool (sealedenvelope.com). The allocation sequence will be stratified by site, age and sex.

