#### Sample size

A comparable study by Briel et al. [18] showed that the number of days when patients experienced restrictions from an ARTI had a standard deviation of 4 days. The PARI project’s non-inferiority design allows for a clinical non-important difference in sickness of max. 1 day in the PCT group compared to the standard care group. We expect an ARTI to last on average 9 days [21, 22]. The power (1-β) is set at 85% and α at 0.025 (non-inferiority study design). We believe these are relevant estimates since non-inferiority of a PCT-guided antibiotic treatment has previously been demonstrated [18, 19].

The two arms of the study will be randomized 1:1 with 231 participants in each arm. We estimate that 10% of participants will not complete the project, so a total of 508 participants will be needed.

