#### Statistical analysis

An intention-to-treat (ITT) and a per-protocol (PP) analysis are planned. Chi-square tests for binary effects and t-test or Mann-Whitney U-test for interval scale effects will be used (depending on distribution).

We will also present descriptive statistics in the different subgroups such as sex, age, and demographic variables.

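### The primary comparison is planned unadjusted; a linear model using the randomisation strata, pre-inclusion illness duration and day-1 CRP would be a free improvement

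*Protocol article*

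**What the plan says.** - Primary outcome: the outcome is labelled "Duration of illness and symptoms from an ARTI". It is then made operational: "The participant-reported primary outcome will be assessed as the number of days until" daily activities are no longer restricted. For the end of the interval, "The recovery measure will be the specific day indicated by the participants using the validated ARTIQ". The margin is one day. The day from which counting starts is not put into words.
- Design, setting and randomization: the allocation is stratified by site, age and sex.
- Interventions and timeline, Day 1: the data collected include "the current infection and the likely focus, duration of illness", and also the CRP level. Day 1 is the day of consent and randomisation, and the later contacts are numbered from it.
- Sample size: SD 4 days, margin 1 day, power 85%, alpha 0.025, 231 per arm. The section adds "We expect an ARTI to last on average 9 days".
- Statistical analysis: intention-to-treat and per-protocol analyses are planned, and "t-test or Mann-Whitney U-test for interval scale effects will be used (depending on distribution"). No covariate or stratum enters the stated comparison.

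**The concern.** The sections on design and on day 1 set up information that the analysis section then does not use. Site, age and sex were important enough to stratify on, and the length of illness before the visit and the CRP level may well predict how long the restriction still lasts. A two-sample test leaves whatever variance these variables explain in the error term. In a non-inferiority trial that widens the interval that has to stay below one day, and so raises the chance of an inconclusive result. The Mann-Whitney option has a further drawback: the test by itself gives no difference in days to set against a margin stated in days.

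A smaller matter is the origin of the day count. If it is left open, the same patient can be given two different durations, because the illness duration recorded on day 1 makes both computable.

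**Working it through.** **Inputs.** From the Sample size section: SD 4, margin 1, alpha 0.025 (taken as one-sided), power 85%, 231 per arm. Assumed: true difference 0, and a multiple correlation r of 0.3 or 0.5 between the covariates and the outcome. The documents give no r.

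**The plan's own figure.** n per arm = 2 × SD² × (z_alpha + z_power)² / margin².
- One-sided 0.025: 2 × 16 × (1.960 + 1.036)² = 287.3, so 288.
- One-sided 0.05: 2 × 16 × (1.645 + 1.036)² = 230.1, so 231.

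The stated 231 therefore follows from one-sided 0.05, not from the stated 0.025. That is a separate matter. It is shown here only because it explains why the starting power below is 77% and not 85%.

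**Effect of adjustment.** Covariates with multiple correlation r leave a residual SD of 4 × √(1 − r²). Power = Φ(1 / (SD × √(2/231)) − z_alpha), with √(2/231) = 0.09305.

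| r | Residual SD | Standard error | Power, one-sided 0.025 | Power, one-sided 0.05 |
|---|---|---|---|---|
| 0 (unadjusted) | 4.00 | 0.372 | Φ(2.687 − 1.960) = 76.6% | Φ(2.687 − 1.645) = 85.1% |
| 0.3 | 3.82 | 0.355 | Φ(2.816 − 1.960) = 80.4% | Φ(2.816 − 1.645) = 87.9% |
| 0.5 | 3.46 | 0.322 | Φ(3.102 − 1.960) = 87.3% | Φ(3.102 − 1.645) = 92.8% |

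The gain is present at either alpha.

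**Time origin.** Let P be the recorded pre-inclusion days and Y the days from day 1. The duration from onset is Y + P. In a linear model containing treatment and P, replacing Y by Y + P changes the coefficient of P by exactly 1 and leaves the treatment coefficient and its standard error unchanged. A simulation agrees (4,000 runs, 231 per arm, SD of Y 4, assumed SD of P 2):

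| Correlation of P and Y | Day 1, unadjusted | Onset, unadjusted | Day 1, adjusted | Onset, adjusted |
|---|---|---|---|---|
| 0 | 77.3% | 66.6% | 77.1% | 77.1% |
| −0.5 | 76.4% | 86.2% | 86.2% | 86.2% |

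**Why no loss from onset counting can be put in figures.** The SD from onset is √(16 + s² + 8 × rho × s), where s is the SD of P, rho is its correlation with Y, and 4 is taken as the SD from day 1. With s = 2 and one-sided 0.025:
- rho = 0: SD 4.47, power 67.1%.
- rho = −0.25: SD 4.00, power 76.6%.
- rho = −0.5: SD 3.46, power 87.3%.

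Neither s nor rho is in the documents, and neither is the origin behind the SD of 4.

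**The case against.** An unadjusted comparison in a randomised trial is valid, and the choice of covariates is commonly left to an analysis plan, which is not shown here. That stands: this is not an error and nothing is biased. But the article does name its test, and the test it names is not the best use of the data it collects. A recommendation is therefore fair.

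The gain also rests on an assumed r. That stands too. If the covariates explain nothing, adjustment gains nothing, but with some 460 patients and a handful of parameters it also costs almost nothing.

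A reader might infer more from the wording: that the text sets two conflicting time origins, and that counting from onset only adds noise and cuts power to 67% or lower. The phrases about the duration of an illness, including "We expect the mean duration of ARTI symptoms to be approximately 9 days", do invite an onset reading. The documents do not support the inference, for four reasons:
- No section says that days are counted from onset. The only day scale starts at inclusion, the outcome sentence reads as looking forward, and the questionnaire appendix that supplies the recovery day is not shown.
- The power figures need an assumed spread of pre-inclusion days and zero correlation with the remaining days. Zero correlation sits badly with treating that duration as a useful predictor. A clearly negative correlation reverses the result.
- If the SD of 4 was itself measured from onset, nothing is lost against the plan.
- Pre-inclusion days do leave the expected difference between arms unchanged, but that says nothing certain about the variance.

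**Conclusion.** The point holds as a free improvement, not as a fault. The stated primary test ignores the stratification factors and two day-1 measurements that the trial already has. With 231 per arm, SD 4, one-sided 0.025 and no true difference, adjustment would raise power from about 77% to about 80% (r = 0.3) or 87% (r = 0.5). Both values of r are assumptions. The figures also take normal theory and a linear covariate effect for granted.

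The missing time origin is a request for clarification. No size can be attached to it from the documents, and it ceases to affect the treatment estimate once pre-inclusion duration is a linear covariate.

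**What to change.** In the Statistical analysis section, make the primary analysis a linear model for the number of days, with treatment, site, age, sex, pre-inclusion illness duration and day-1 CRP. Report the adjusted difference between arms in days with its confidence interval, and compare the upper limit with one day, in both the intention-to-treat and the per-protocol analysis. Fix the covariates and their form before any data are compared by arm. The unadjusted comparison can stay as a supporting analysis.

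In the Primary outcome section, add one sentence saying that days are counted from randomisation (day 1). In the Sample size section, confirm that the SD of 4 days uses the same origin.

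The cost is a few sentences and a routine model. The data are already collected, and no extra visit, measurement or patient is needed.

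### No recovery question is listed after day 15, so participants still restricted then never supply the primary outcome, and a comparison of mean days would understate a real prolongation

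*Protocol article*

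**What the plan says.** Under Primary outcome, the article measures "the number of days until a patient’s daily activities (e.g. work and recreation) are no longer restricted by symptoms from an ARTI", with a one-day non-inferiority margin, and adds: "The recovery measure will be the specific day indicated by the participants using the validated ARTIQ".

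The contact schedule is given in two places. The caption of Table 1 reads "Shows the interventions in both the intervention and the control group at days 1, 3, 5, 7 and 15", and the table marks the ARTIQ on all five days. Under Interventions and timeline, "Each participant will be sent a link to the ARTIQ by e-mail on days 3 and 7"; telephone interviews on days 5 and 15 cover, among other things, "days unable to work, the results of the ARTIQ, and compliance". Day 30 is described as "An administrative follow-up to gather information about the use of antibiotics and hospital admissions". No recovery item is listed there.

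Under Sample size: "We expect an ARTI to last on average 9 days", with an SD of 4 days, one-day margin, α 0.025, power 85% and 231 participants per arm. Under Statistical analysis, interval-scale outcomes are compared by t-test or Mann-Whitney test, depending on distribution. No rule is given for someone still restricted at day 15.

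**The concern.** The trial must rule out that PCT guidance lengthens illness by a day or more. Long illnesses carry much of the information on that question, and follow-up for the primary outcome stops while some of them are still running. With a mean of 9 and an SD of 4 days, day 15 is only 1.5 SD above the mean.

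If the PCT arm really does worse, more of its participants pass day 15 unrecovered. Setting them to 15 or leaving them out removes more illness time from that arm than from control. The difference in means shrinks towards zero, and in a non-inferiority trial that makes a false declaration of non-inferiority more likely.

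A second, lesser matter is the eight-day interval between the day-7 and day-15 contacts. It spans the 9-versus-10-day contrast that the trial is meant to resolve, so recovery dates inside it rest on recall.

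**Working it through.** **Inputs from the article.** Mean 9 days, SD 4, margin 1 day, α 0.025 (taken as one-sided), 231 per arm; ARTIQ on days 1, 3, 5, 7 and 15; no recovery item at day 30.

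**Assumptions.** Days are counted from day 1. The distribution is not given, so normal, gamma and lognormal shapes were used, each with mean 9 and SD 4. The longer arm has mean 10, with either the same SD of 4 (uniform) or SD 4 × 10/9 = 4.44 (proportional).

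**The plan's own figure.** n per arm = 2 × SD² × (z_α + z_β)² / margin². With one-sided 0.025: 32 × (1.960 + 1.036)² = 287.3, so 288. With one-sided 0.05: 32 × (1.645 + 1.036)² = 230.1, so 231. The stated 231 thus matches 0.05 rather than 0.025. That is a separate matter; 231 is used below because it is the planned number.

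**Who passes day 15.** Normal, mean 9: z = (15 − 9)/4 = 1.5, so 6.7%. Gamma gives 8.1% and lognormal 7.8%. In the longer arm, normal: uniform z = 5/4 = 1.25, so 10.6%; proportional z = 5/4.44 = 1.125, so 13.0%. Across shapes the longer arm has about 11–13%.

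**Effect on a mean comparison when the true difference equals the margin.** Let d be the expected difference after the day-15 rule. The chance of declaring non-inferiority is Φ((1 − d)/SE − 1.96), which should be 2.5%.

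Example (normal, uniform, set to 15): d = 0.915, SDs 3.76 and 3.64, SE = √(3.76²/231 + 3.64²/231) = 0.344. Then (1 − 0.915)/0.344 − 1.96 = −1.71, and Φ = 4.3%.

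| Longer arm | Shape | Set to 15: d | False NI | Dropped: d | False NI |
|---|---|---|---|---|---|
| Uniform | normal | 0.915 | 4.3% | 0.738 | 12.0% |
| Uniform | gamma | 0.915 | 4.5% | 0.794 | 10.4% |
| Uniform | lognormal | 0.920 | 4.5% | 0.815 | 10.0% |
| Proportional | normal | 0.827 | 7.0% | 0.472 | 32.5% |
| Proportional | gamma | 0.801 | 8.8% | 0.532 | 33.9% |
| Proportional | lognormal | 0.806 | 9.2% | 0.584 | 32.1% |

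When dropping, n per arm is 231 times the share recovered by day 15. Repeat simulations move these figures by about a point at most.

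**With follow-up to day 30**, and 30 assigned to anyone unrecovered, the expected difference is 0.99–1.00 day and false non-inferiority 2.4–2.6% in the same scenarios.

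**Sensitivity to the time origin.** If the 9 days run from onset and the mean from day 1 is 6–7 days (assumption, SD 4), 1–5% of controls pass day 15. The same formula with a uniform shift gives about 3–4% when set to 15 and 4–7% when dropped. With a proportional shift it gives about 4–7% and 13–24%.

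**Recall interval.** Normal, mean 9: Φ(1.5) − Φ(−0.5) = 0.933 − 0.309 = 62.5% recover between days 7 and 15. Gamma and lognormal give 57%. With a mean of 6–7 days, 25–48% do.

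**The case against.** - **The analysis plan may deal with this.** A journal article commonly leaves censoring rules to the full protocol or SAP, so the lack of a rule is not itself a fault. A reader might infer that the slowest patients will be dropped; the article does not say so, and the dropped column is conditional on that choice. But the contact schedule is stated, and no rule creates dates that were never asked for. Treating these patients as censored at day 15 does not help a difference in means: the restricted mean to day 15 equals the mean with values set to 15.
- **A rank test copes.** This stands. If the unrecovered share the top rank, the probability that a PCT patient is ill longer moves only from 0.5703 to 0.5701 under a uniform shift. The article allows Mann-Whitney. However, a rank test does not by itself express the result in days against a one-day margin.
- **Days 7 to 15 are not unobserved.** This also stands. A participant who recovers on day 10 can name that day at the day-15 contact. A reader might infer that the gap itself biases towards non-inferiority. The documents do not support that: both arms share the schedule and participants are not told their allocation, so recall error is noise with no shown direction.
- **The size rests on the time origin.** Correct, as the sensitivity figures show. That most recoveries fall in the gap holds only if the 9 days run from day 1.
- **Larger bias figures need an unsupported scenario.** If 10% were ill 10 days longer, false non-inferiority would be about 21–22% when set to 15 and 75% or more when dropped. Nothing in the article supplies that pattern.
- **Late illness is partly visible.** Re-consultations, antibiotic use and admissions are counted to 30 days. They do not supply a recovery date.

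**Conclusion.** The point holds for the day-15 cut-off. As listed, the schedule cannot give a recovery day for participants still restricted at day 15, and a mean comparison built on it leans towards non-inferiority. The lean is modest if values are set to 15 and substantial if they are dropped. The figures assume mean 9 and SD 4 from day 1, a true difference equal to the margin, and 231 analysable per arm before any are dropped. A shorter mean from day 1 reduces them, and a rank analysis largely avoids the problem. The day-7 to day-15 interval is a matter of precision only. The change is worth making because it is cheap and restores the intended error rate, not because the primary result is shown to be invalid.

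**What to change.** Keep sending the existing e-mailed recovery-date question, at regular intervals, to anyone still restricted at day 15, until recovery or day 30. In the analysis, give those known to be unrecovered at day 30 a value of 30 days, rather than dropping them or setting them to 15. Treat people who do not report as missing, not as recovered. State whether days are counted from symptom onset or from day 1.

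Optionally, add one or more recovery-date e-mails between days 7 and 15 to shorten recall.

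Cost: a minor amendment, a few automated messages through the survey system already in use, and slightly more participant burden. The messages after day 15 go only to a small minority.

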#### Secondary outcomes

These are the outcomes to be assessed regarding antibiotic treatment and clinical measures of treatment failure:

Number of participants in each trial arm exposed to antibiotic treatment at index consultation (day 1) and within 30 days.Number of participants in each trial arm with side effects from antibiotic treatment within 14 days.Number of participants in each trial arm with re-consultations within 30 days.Number of participants in each trial arm admitted to hospital (including diagnosis and mortality) within 30 days.Characterization of biomarker (CRP and PCT) level at index consultation..

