#### Guidance for PCT levels

PCT levels are guided by current literature [16, 17, 26] as follows:

PCT-levels between < 0,25 ng/mL: low risk of bacterial etiology, antibiotic treatment will not be prescribed.PCT levels $$\ge$$ 0,25: bacterial etiology is more likely, antibiotic treatment will be prescribed

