## Discussion

The PARI project is, to our knowledge, the first study to examine a PCT POC test in general practice. Previous studies have examined PCT levels either in a hospital setting or in general practice with a venous blood sample and a prolonged wait for the result. GPs are familiar with POC tests (such as CRP and strep A tests) and these are valuable tools for decision-making in many cases. However, application of PCT as an add-on when an ARTI is not trivial (e.g. CRP values are above 20 mg/L), may aid the GP in ruling out a serious bacterial infection. This could in theory limit GP uncertainties and assist in targeting antibiotics only to the relatively few patients with a high probability of having a bacterial infection and likely to benefit from antibiotic treatment. If this study shows that the PCT-guided antibiotic treatment for ARTI can reduce the use of antibiotics with no safety concerns for the patients (i.e. prove non-inferiority), it will contribute to reaching national goals for improving the rational use of antibiotics in general practice and thereby reduce the development of antibiotic resistance.

Strengths of the study include the randomized controlled trial design that will provide a clear answer regarding the study’s primary objectives. A non-inferiority design has been chosen to examine whether a PCT POC test is not worse than standard care regarding patient safety and duration of symptoms. In addition, we expect PCT testing to reduce the number of antibiotic prescriptions.

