There are some limitations to the study. First, the study is single-blinded, i.e. patients are unaware of the treatment group to which they have been randomized. This is important to minimize reporting bias in the PARI trial as the primary outcome is a patient-reported outcome (recovery). It is impossible in this setup to blind GPs since they need to know which group the patient is randomized to as part of the clinical decision-making process. This information bias could lead to the GP learning from the results of the PCT test and thereby improving their clinical judgement. However, we do not believe such a bias will significantly change the results of the study and the direction of the bias would likely be conservative. Second, the GPs who opt to be included in this study may be more motivated and interested in research and they may be more reluctant to prescribe antibiotics in general, compared to other GPs. This kind of selection bias could affect the results. However, the direction of this bias is also likely to be conservative.

Another limitation to consider is that the analysis of a PCT POC test takes 20 min compared to the CRP measurement, which only takes a couple of minutes. In this study setting we do not consider this a problem, but in the longer term, it could affect the practical use and possible implementation of findings on a wider scale in general practice.

In conclusion, the PARI study is, to our knowledge, the first to examine a PCT POC test in general practice aimed at reducing the use of antibiotics in patients with symptoms of ARTI, without prolonging the symptoms and the duration of restrictions to patients’ daily lives. Since antibiotic resistance is a worldwide health problem, we believe that the results of this study could help to better target antibiotic treatment only to those patients with bacterial infections, which in turn will contribute to limiting antibiotic resistance.

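### Secondary outcome 2 counts only antibiotic-attributed side effects, judged with knowledge of treatment, so any misattribution of illness symptoms tilts the arm comparison towards PCT

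*Protocol article*

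**What the plan says.** The Secondary outcomes section of the protocol article gives as its second item "Number of participants in each trial arm with side effects from antibiotic treatment within 14 days". The item before it is "Number of participants in each trial arm exposed to antibiotic treatment at index consultation (day 1) and within 30 days", so antibiotic exposure is itself something the trial expects to affect. Two other places give the direction. Under Guidance for PCT levels, a result below the threshold means "low risk of bacterial etiology, antibiotic treatment will not be prescribed". The Discussion states: "In addition, we expect PCT testing to reduce the number of antibiotic prescriptions".

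On blinding, the Design section says "The PARI project is a single-blinded study as participants will not be informed of their allocation group", and the Discussion says "It is impossible in this setup to blind GPs since they need to know which group the patient is randomized to". Participants are therefore masked to allocation but not to whether they were given an antibiotic, and no placebo antibiotic is described.

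On data collection within the 14-day window, all participants are telephoned on days 5 and 15 for "follow-up on their clinical condition (changes in general condition, fever, pain or coughing), days unable to work, the results of the ARTIQ, and compliance". On analysis, the Statistical analysis section specifies "Chi-square tests for binary effects", with intention-to-treat and per-protocol analyses planned.

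**The concern.** The numerator depends on a causal judgement that can be made only for treated participants. These patients are all acutely unwell, so some will have symptoms that could be read either as the infection or as a drug effect. In a treated participant such a symptom may be counted. The same symptom in an untreated participant never can be. Because the control arm is expected to have more treated participants, any such mislabelling falls more often on the control arm.

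At stake is how a favourable result on this outcome may be read. A lower count in the PCT arm could reflect fewer real side effects, fewer opportunities to mislabel illness as a side effect, or both. The attributed count alone cannot tell these apart. The primary outcome is not affected.

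**Working it through.** **Inputs from the article.** 231 participants per arm, 1:1 (Sample size); chi-square test for binary outcomes (Statistical analysis); fewer prescriptions expected under PCT (Discussion). The article states no figure for this outcome, so there is none to reproduce.

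**Assumed inputs, since the article gives none.** Antibiotic exposure *e* in each arm; *b*, the share of participants with an illness symptom that would be attributed to the antibiotic if one had been taken; *s*, the true antibiotic side-effect rate among the treated. The test is the uncorrected chi-square at two-sided 5%.

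**Step 1: recorded rate under the stated definition.** Recorded rate in an arm = *e* × (*b* + *s* − *bs*). With *s* = 0 this is *e* × *b*, and the spurious difference is (*e* control − *e* PCT) × *b*. It is zero if *b* = 0 or if exposure is equal.

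**Step 2: chance of a significant result when antibiotics cause no side effects, exposure 60% v 40%.**

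| *b* | Control v PCT rate | Expected counts of 231 | Test rejects |
|---|---|---|---|
| 0 | 0 v 0 | 0 v 0 | never |
| 2% | 1.2% v 0.8% | 2.8 v 1.8 | about 6% |
| 5% | 3% v 2% | 6.9 v 4.6 | about 10% |
| 10% | 6% v 4% | 13.9 v 9.2 | about 16% |
| 20% | 12% v 8% | 27.7 v 18.5 | about 30% |

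At *b* = 5%, 10% and 20%, other exposures give 16%, 29% and 55% (70% v 40%) and 8%, 12% and 21% (50% v 35%). With a continuity correction the 60/40 figures fall to about 12% at *b* = 10% and 25% at *b* = 20%, and the inflation at *b* = 5% is slight. When the same symptoms are counted in everyone and *s* = 0, the rates are equal and the test rejects in about 5%.

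**Step 3: when antibiotics do cause side effects.** Take *s* = 10%, *b* = 10%, exposure 60% v 40%.
- Recorded difference: 0.2 × (0.10 + 0.10 − 0.01) = 3.8 points.
- Difference in participants with a true antibiotic side effect: 0.2 × 0.10 = 2.0 points.
- Difference in participants with any such symptom, whatever the cause: 0.2 × 0.10 × 0.9 = 1.8 points.

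The recorded difference is about twice the true one.

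**Step 4: why the attributed count cannot resolve this.** Rates of 6% v 4% arise from *s* = 0 with *b* = 10%, and equally from *s* = 10% with *b* = 0. The data on this outcome would look the same in both cases.

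**Step 5: price of counting everyone.** The all-participant rate is *b* + *e* × *s* × (1 − *b*). For *s* = 10%, *b* = 10%, 60/40 this is 15.4% v 13.6%, with power about 9%. Correctly attributed events (6% v 4%) give about 16%. For *s* = 20%, *b* = 10%, 70/40, power is about 31% (22.6% v 17.2%) against about 55% (14% v 8%).

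**The case against.** The strongest reply is that the outcome means what it says: only side effects caused by the antibiotic count, which on its face excludes illness symptoms. PCT guidance can reduce such harm only by reducing exposure, so a count that follows exposure reflects the intended mechanism. The denominator is everyone randomised, so randomisation is preserved. This stands. If attribution is valid, the comparison is legitimate and unbiased.

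A reader might infer more than the document supports on three points.

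- *That illness symptoms will score in treated patients, so that the control arm will look worse even if antibiotics are harmless.* The article does not say that misattribution will occur or how often. At 2% the inflation is negligible.
- *That nothing is asked of everyone.* The interviews do put questions on general condition, fever, pain and cough to all participants, and the ARTIQ goes to everyone. Its items are in an appendix not shown here and may overlap with possible side effects.
- *That the attributed comparison should be dropped.* Step 5 shows what that would cost in power.

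It is also fair to say that side-effect forms and attribution rules usually sit in a fuller protocol, so their absence from an article is not a fault. But a better form would not alter the stated definition, which keeps untreated participants out of the count, nor the fact that treated participants know they were treated.

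**Conclusion.** The point holds conditionally. The definition makes scoring possible only for the treated, exposure is expected to differ by arm, and attribution is made knowing whether an antibiotic was taken. Any misattribution of illness symptoms therefore biases the comparison towards PCT. How far is unknown. Under the assumed 60% v 40% exposure with no true side effects, the false-positive rate runs from about 6% (2% misattributed) to about 30% (20% misattributed), and there is no bias with perfect attribution. The document does not support the stronger claim that this outcome cannot show whether PCT guidance spares patients harm. What it supports is that a lower attributed count is not sufficient evidence of that on its own. This is a worthwhile improvement to one secondary outcome and does not touch the primary conclusion.

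**What to change.** In the existing day-5 and day-15 interviews, put one fixed list of possible side effects to every participant in both arms, in the same words and whether or not an antibiotic was taken. Compare the number of participants with any item on the list between arms, among all randomised participants. Report this beside the antibiotic-attributed count per arm. State in the plan that the attributed count rests on attribution made with knowledge of treatment and is not by itself evidence of less harm.

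The cost is a few extra questions in calls already scheduled and one or two sentences in the plan. The drawback is that the all-participant measure includes background symptoms and has materially lower power (Step 5), so a null result on it would say little. For that reason it should sit alongside the attributed count and not replace it.
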